## Randomization

Randomization is stratified by site and occurs at the patient level to allocate participants to each of the 2 study arms in a 1:1 ratio, using permuted block randomization that is integrated into the web-based data collection system.

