## Sample Size Calculation

We based our sample size on the standardized mean differences (Cohen’s d) for the co-primary outcomes of knowledge (0.46) and decisional conflict (0.36) reported in the 2014 Cochrane review of decision aid RCTs. Assuming two-sided alpha levels of 0.025 (for each co-primary outcome) and 15% attrition, 175 women per arm afforded us 80% power to detect these differences.

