## Covariates and Baseline Characteristics

| Covariate                          | Description                                                                                                                                                                                                                                       | Time Point       | Variable Structure                                                                                                                  | Structure for Analysis                                                                                                              |
|------------------------------------|---------------------------------------------------------------------------------------------------------------------------------------------------------------------------------------------------------------------------------------------------|------------------|-------------------------------------------------------------------------------------------------------------------------------------|-------------------------------------------------------------------------------------------------------------------------------------|
| Future pregnancy desires           | Do you want to get pregnant in the future?"

Note: this was measured in the decision aid for intervention group and at the very beginning of T1 assessment for control group                                                                | BL               | Ordinal (1-5)

Definitely no (1)
Probably no (2)
Not Sure/Fine Either Way (3)
Probably Yes (4)
Definitely Yes (5) | Ordinal (1-5)

Definitely no (1)
Probably no (2)
Not Sure/Fine Either Way (3)
Probably Yes (4)
Definitely Yes (5) |
| Intendedness of Current Pregnancy* | Unintended= Unwanted (did not want baby then or in future) or got pregnant sooner than wanted                                                                                                                                                     | BL               | See below                                                                                                                           | See below                                                                                                                           |

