|-------------------------------------------------------|-----------------------------------------------------------------------------------------------------------------------------------------------------------------------------------------------------------------------------------------|--------------------------------------------------------------|---------------------------------------------------------------------------------------------------------------------------------------------------------------------------------------------------------------------------------------------------------------------------------------------------------------------------------------------------------------------------------------------------------------------------------------------------------------------------------------------------|------------------------------------------------------------------------------------------------------------------------------------------------------------------------------------------------------------------------------------------------------------------------------------------------------------------------------------------------|
| Desire for sterilization                              | At this point, how do you feel about sterilization? 5-point Likert (I definitely don't want sterilization, I probably don't want sterilization, neutral/not sure, I probably do want sterilization, I definitely do want sterilization) | T1 for controls + before Decision Aid for intervention group | Ordinal (5-point Likert)                                                                                                                                                                                                                                                                                                                                                                                                                                                                          | 
This can be measured two ways:
 
1) Continuous (1-5)
 
2) Ordinal:
           Definitely don't (1)
           Probably don't (2)
           Not sure (3) = 3
           Probably do (4)
           Definitely do (5)
 
Group differences at baseline (pre-DA for intervention group, T1 for control)
 |

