## Statistical Analyses

### Descriptive and Baseline Statistics

All primary and secondary outcomes will be described using sample means or proportions along with accompanying confidence intervals. Suitable transformations will be considered for continuous variables if there are substantial departures from normality. Baseline characteristics will be compared between the study arms using two-sample t-tests or chi-square tests, as appropriate (see Outcome Variables tables above).

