### Exploratory Hypotheses

For the following exploratory hypotheses, regression will be used to test intervention effects controlling for study site. The beta coefficient and corresponding 97.5% confidence interval will be used to assess the effect of the intervention.

- **Pre- and Post-Dobbs SCOTUS Decision Exploratory Analyses:** regression analyses are adjusted for study site  
\*\*note state interaction effects below\*\*
  - Date for the *Dobbs* decision can be categorized in 3 ways:
    - Dichotomized as before June 24, 2022 and June 24, 2022 or later (the verdict)
    - Dichotomized as before May 1, 2022 and May 1, 2022 or later (the leak)
    - Categorical: before May 1; May 1- June 23; June 23 or later (would measure effect of the leaked news and then effect of the full impact)
  - How did the *Dobbs* SCOTUS decision impact recruitment?
    - Recruitment changes pre- and post-Dobbs
      - More interest in joining study
      - Differences in recruitment across gravida and parity
  - How has it affected our outcomes of interest?
    - The desire for sterilization at baseline
    - Decisional conflict about contraceptive method selection at T1 predicted by date
    - Ease in contraceptive decision making at T1 and T2 predicted by date
    - Certainty about sterilization decision at T1 and T2 predicted by date
    - Contraceptive method selected at T1 and T2 predicted by date
    - Contraceptive method used at T3 predicted by date

- **\*\*Interaction effect between date and state on all outcomes (for every outcome)\*\***

- **Additional Sensitivity Analyses for Primary and Secondary Outcomes**

- We will run additional sensitivity analyses to test robustness of the intervention effects after adjusting for any significant differences in baseline characteristics (to be identified during analysis) between the intervention and control group that are also associated with the outcomes of interest:
  - 1) sterilization knowledge at T1
  - 2) decisional conflict at T1
  - 3) contraceptive method selected at T1
  - 4) satisfaction with decision-making at T3
- We will run additional sensitivity analyses to test robustness of the intervention effects after adjusting for differences in:
  - T3 Outcomes (satisfaction with decision-making at T3):

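### The adjusted sensitivity analyses choose covariates by significance tests during analysis, from a table that includes two items asked after randomisation; a fixed list of pre-randomisation prognostic variables would serve better

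*Combined protocol and SAP*

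**What the plan says.** Under Primary and Secondary Hypotheses, the four main models are intention-to-treat linear or logistic regressions adjusted for study site only. Site is the randomisation stratum.

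Under Descriptive and Baseline Statistics, "Baseline characteristics will be compared between the study arms using two-sample t-tests or chi-square tests". No significance level is stated.

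Under Exploratory Hypotheses, the additional sensitivity analyses of knowledge, decisional conflict and method selected at T1, and satisfaction at T3, are run "after adjusting for any significant differences in baseline characteristics (to be identified during analysis) between the intervention and control group". The sentence goes on to a second condition: the variable must also be associated with the outcome. Neither significance nor association is defined, and no variables are named.

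The section on baseline, intervention and T1 procedures puts randomisation after the baseline interview and before both the decision aid and T1. Two entries in the Covariates and Baseline Characteristics table do not fit that order:

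- **Future pregnancy desires** is labelled BL, but its note says "this was measured in the decision aid for intervention group and at the very beginning of T1 assessment for control group". The Variables summary table marks it under T1, and that table's footnote says it was measured before and after the aid in the intervention arm.
- **Desire for sterilization** is timed as "T1 for controls + before Decision Aid for intervention group", and the table uses it to compare the arms at baseline.

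**The concern.** In a randomised trial, a significant arm difference in a true baseline variable arises by chance. Its p-value says nothing about how well the variable predicts the outcome, and prediction is what makes adjustment useful. A strong predictor that is balanced fails the test and is left out. The second condition removes variables unrelated to the outcome, but it has to be checked against outcome data during analysis. The covariate set can therefore differ between the four outcomes and is unknown until the data are open. A robustness check of that kind reassures less than one fixed in advance.

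The two items asked after randomisation raise a different problem. For them an arm difference need not be chance, so the screen is more likely to pick them up when allocation has influenced the answers. Both plausibly relate to method selected, a secondary outcome. Adjusting for a variable that allocation has moved can take out part of the effect being estimated.

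At stake are the value of the adjusted analyses as a check, and precision that could be had from data already collected. The validity of the confirmatory tests is not at stake.

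**Working it through.** **Inputs from the plan.** Sample Size Calculation: d = 0.46 (knowledge) and d = 0.36 (decisional conflict), "Assuming two-sided alpha levels of 0.025 (for each co-primary outcome) and 15% attrition", and "175 women per arm afforded us 80% power to detect these differences". Randomization is 1:1.

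**Reproducing the plan's figure.** With SD = 1, n per arm = 2(z₁ + z₂)²/d², where z₁ = 2.241 (two-sided 0.025) and z₂ = 0.842 (80% power).
- d = 0.36: 2 × 3.083²/0.1296 = 146.7, so 147 evaluable; 147/0.85 = 173 enrolled, against 175 stated.
- d = 0.46: 90 evaluable; 90/0.85 = 106 enrolled.

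The stated size reproduces, and decisional conflict drives it. 175 × 0.85 = 148.75, about 149 evaluable per arm.

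**What a fixed prognostic set could add.** If the covariates explain a share R² of the within-arm variance, the residual SD is √(1 − R²) and the effective d is d/√(1 − R²). The plan gives no R², so a range is assumed. Power by two-sample t-test, alpha 0.025:

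| R² | SE reduction | d = 0.36, 149/arm | d = 0.36, 175/arm |
|---|---|---|---|
| 0 | – | 0.803 | 0.867 |
| 0.05 | 2.5% | 0.825 | 0.885 |
| 0.10 | 5.1% | 0.846 | 0.902 |
| 0.20 | 10.6% | 0.888 | 0.935 |
| 0.30 | 16.3% | 0.927 | 0.962 |

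For knowledge (d = 0.46), unadjusted power is already 0.957 at 149 per arm and 0.980 at 175.

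**What the plan's rule delivers.** Simulation of 4,000 trials per setting, 148 per arm, continuous outcome, 23 independent baseline covariates of which 4 are prognostic (joint R² as shown). A covariate enters if both its arm difference and its association with the outcome have p < 0.05. The treatment test is at 0.025. The covariate count and the 5% levels are assumptions.

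| R² | Any covariate enters (d = 0 / 0.36) | Type I error: none / rule / fixed | Power at d = 0.36: none / rule / fixed |
|---|---|---|---|
| 0.10 | 18% / 20% | 0.025 / 0.023 / 0.023 | 0.80 / 0.80 / 0.83 |
| 0.20 | 20% / 24% | 0.030 / 0.027 / 0.025 | 0.80 / 0.80 / 0.89 |
| 0.30 | 22% / 23% | 0.027 / 0.020 / 0.025 | 0.80 / 0.81 / 0.93 |

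The Monte Carlo standard error at 0.025 is √(0.025 × 0.975/4000) = 0.0025. The rule does not inflate type I error, and it leaves nearly all the available precision unused.

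**The two items asked after randomisation.** The simulation covers only true baseline variables, so these are judged from the text. The covariate version of desire for sterilization is asked before the aid, or at the start of T1 in controls. The aid's content cannot have shaped it; knowledge of allocation could. Future pregnancy desires is asked inside the aid according to the covariate table, so the aid's content may have influenced it, and the mode of asking differs by arm. The Variables footnote gives a different timing, and the two statements must be reconciled. The documents give no figure from which to size the bias.

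**The case against.** The strongest reply is about scope. The rule governs only sensitivity analyses listed under Exploratory Hypotheses. A reader might infer that the main analysis is data-driven or its error rate inflated. The documents do not support that: the four main models are fixed in advance with site alone, and even within the sensitivity analyses the simulation shows no inflation.

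A reader might also reason that about 25 baseline items tested at 5% give a 1 − 0.95²⁵ = 72% chance of a spurious covariate. That is the chance of at least one significant baseline test, assuming independence. It is not the chance that a covariate enters, because the outcome condition must also be met; the simulation puts that at 18% to 24%. Neither the 5% level nor the count is in the plan, and independence is doubtful for pairs such as gravida and parity.

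The precision argument can be overstated too. No document shows that education, literacy, parity or counselling predicts either outcome. Both co-primary outcomes are measured at T1, planned for the same session as randomisation where possible, so evaluable numbers may be nearer 175 than 149 and power nearer 0.87 before any adjustment. Knowledge has little to gain.

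Finally, the plan does not name either of the two items as an adjuster; each would have to pass both conditions, and the risk is smaller for desire for sterilization.

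All of this stands and limits the point. It does not justify the rule: a check on robustness to prognostic imbalance is better run with prognostic variables named beforehand, and nothing in the plan keeps the two items out.

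**Conclusion.** The point holds as a matter of analysis choice in the sensitivity analyses. The confirmatory tests are sound. The selection rule depends on the data, omits balanced predictors, and yields power of 0.80 to 0.81 where a fixed set would give 0.83 to 0.93 under the simulated R² of 0.10 to 0.30. Analytically, for decisional conflict, R² of 0.05 to 0.30 takes power from 0.80 to between 0.825 and 0.93 at 149 per arm, or from 0.87 to between 0.885 and 0.96 at 175. These gains rest wholly on the assumed R² and matter mainly for decisional conflict.

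Two items treated as baseline are collected after randomisation. Bias from adjusting for them is possible but not demonstrated, and it is likelier for future pregnancy desires than for desire for sterilization. The change is worth making; the trial does not fail without it.

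**What to change.** 1. Remove the significance screen from the sensitivity analyses. Describe baseline characteristics by arm without tests.
2. Before arm-level outcomes are examined, name a short list of prognostic variables collected in the baseline interview: for example age, parity, education, health literacy, sterilization counselling reported at BL, and Medicaid consent signed at BL.
3. Fit that list with site as the single adjusted sensitivity model for all four outcomes. Alternatively, put it in the primary and secondary models for precision, which is the larger change. For method selected, report a standardised risk difference as well, since odds ratios under different adjustment are not directly comparable.
4. Exclude future pregnancy desires and desire for sterilization from adjustment, and label both as collected after randomisation.
5. Reconcile the covariate table with the Variables table and its footnote on when future pregnancy desires was asked.

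The cost is SAP wording; the data are already collected and the sample size is unchanged. The list must be settled before unblinded outcomes are seen, and a few missing covariate values will need simple imputation. Moving the two questions into the baseline interview would not be a wording change: the documents describe those measurements in the past tense, so earlier participants could not be asked again.

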### Intervention arm

Participants randomized to the intervention arm use our novel web-based tool prior to 24 weeks gestation. As all women requesting a Medicaid-funded procedure must adhere to the federal consent process, women in the intervention arm who remain interested in undergoing sterilization as they proceed through pregnancy must complete the consent process as per usual care. Thus, our intervention arm is decision aid plus usual care.

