## Intervention and Timepoints

### Baseline, Intervention, and Time 1 Assessment

Immediately (when possible) after consent, study staff will conduct baseline interviews to assess patient demographic characteristics as well as medical and reproductive history. All assessments will be administered as interviews by study staff who enter the data into REDCap. Women will then be randomized to one of the 2 study arms using computer-generated allocation that is incorporated into the study database. Those randomized to the control (usual care) condition will immediately complete their Time 1 assessment (in person or via phone) to assess knowledge, contraceptive method selected, and decisional conflict. After the baseline survey, those randomized to the intervention arm immediately will use the decision aid on a phone, tablet, or computer. Participants randomized to the decision aid will receive a summary sheet (via email or printout) of their responses, which they are encouraged to share with their healthcare provider. Study staff members will be available throughout to assist participants as needed to answer questions. Following completion of the intervention, staff will then conduct the T1 assessment with the participants. Study procedures at this initial time point will take a total of 60-90 minutes for women in the intervention group and 30-45 minutes for those in the usual care arm.

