| Right before you got pregnant with this pregnancy, did you want to have a baby at any time in the future?                                                                                                                                         | X  |    |    |    |
| Would you say you got pregnant sooner, about the right time, or later than you wanted?                                                                                                                                                            | X  |    |    |    |
| On a scale of 0-10, where 0 means you were very unhappy to be pregnant and 10 means that you were very happy to be pregnant, tell me which number best describes how you felt when you found out you were pregnant?                               | X  |    |    |    |
| On a scale of 0-10, where 0 means trying hard not to get pregnant, and 10 means trying hard to get pregnant, if you had to rate how much you were trying to get pregnant or avoid pregnancy before you got pregnant, how would you rate yourself? | X  |    |    |    |
| Signed Medicaid consent                                                                                                                                                                                                                           | X  |    | X  | X  |
| Desire for sterilization*                                                                                                                                                                                                                         |    | X  |    |    |
| Thoughts of sterilization before (and reasons for not)                                                                                                                                                                                            | X  |    |    |    |
| Received any provider contraceptive counseling                                                                                                                                                                                                    | X  |    | X  |    |
| Received any provider sterilization counseling during current pregnancy                                                                                                                                                                           | X  |    | X  | X  |

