    - Provider sterilization counseling between T1 and T3 (composite variable of this question at T3 about counseling during this pregnancy isolating those who said they already received this counseling prior to or during this pregnancy at baseline)
    - Provider contraceptive counseling between T1 and T3
    - Medicaid consent signed between T1 and T3
    - Provider sterilization and/or Medicaid consent between T1 and T3

- **Subgroup Analyses (Interactions, no *a priori* hypothesis, not powered) of the Primary Outcomes by:**

*Regression model needs to control for site, including direct effects of the decision aid and the variable of interest below. Check for collinearity (VIF with a cut-off of 10)*

- Race/ethnicity (non-Hispanic Black, non-Hispanic White, Hispanic, non-Hispanic Other)
  - **Knowledge=decision aid + site + race/ethnciity + DA#Race/ethnicity**
  - **Decisional conflict= decision aid + site + race/ethnciity + DA#Race/ethnicity**
- Age (categorized for this analysis: <25, 25+)
  - **Knowledge= decision aid + site + age + DA#age**
- Completed Decision Aid in-person or virtual
- Recruitment Site (California, Pennsylvania, Tennessee)
- Language of the consent form (English vs Spanish)
- Education level (HS or less including GED vs. any post-high school or more)
- Provider counseling/consent form signed at T1
  - Provider sterilization counseling at baseline (before this pregnancy, during this pregnancy)

- **Participant Satisfaction with Current Contraceptive Method(s) at Time 3:** Compared to women who receive usual care alone, women randomized to the decision aid arm will report greater satisfaction with their current contraceptive method(s) at Time 3

- **Desire for sterilization:** variable will be used to assess baseline differences (pre-decision aid for intervention group, T1 for control), changes from baseline to T1 for intervention groups, and differences between post-decision aid for intervention group vs T1 for control group.

- To test exploratory hypotheses, we will first use linear regression (using the continuous measure 1-5 where higher score indicates higher desire for sterilization) to test intervention effects (pre-intervention baseline vs post-intervention T1; post-intervention vs T1 control), controlling for study site.

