- We will also use ordinal regression (using the recoded 3, 4, and 5 values where higher score indicates higher strength of desire but not for/against sterilization) to test intervention effects controlling for study site.

- **Participant Knowledge about Tubal Sterilization at Time 2:** Compared to women who receive usual care alone, women randomized to the decision aid arm will have greater knowledge about sterilization and alternative options at T2.

- ***Sensitivity Analyses:*** We will run sensitivity analyses to test robustness of the intervention effects after adjusting for differences in:
  - Provider sterilization counseling between T1 and T2 (“since our last meeting”)
  - Provider contraceptive counseling between T1 and T2 (“since our last meeting”)
  - Medicaid consent signed between T1 and T2 (“since our last meeting”)
  - Provider sterilization and/or Medicaid consent signed between T1 and T2 (“since our last meeting”)
- **Participant Decisional Conflict in Postpartum Contraceptive Choice at Time 2:** Compared to women who receive usual care alone, women randomized to the decision aid arm will have lower decisional conflict in postpartum contraceptive choice at Time 2
- ***Sensitivity Analyses:*** We will run sensitivity analyses to test robustness of the intervention effects after adjusting for differences in:
  - Provider sterilization counseling between T1 and T2 (“since our last meeting”)
  - Provider contraceptive counseling between T1 and T2 (“since our last meeting”)
  - Medicaid consent signed between T1 and T2 (“since our last meeting”)
  - Provider sterilization and/or Medicaid consent signed between T1 and T2 (“since our last meeting”)
- **Contraceptive Method Selected at Time 2:** Compared to women who receive usual care alone, women randomized to the decision aid arm will be less likely to select sterilization at T2 and more likely to select an alternative method
- **Contraceptive Method(s) Used at Time 3:** Compared to women who receive usual care alone, women randomized to the decision aid arm will be less likely to select sterilization at T3 and more likely to select an alternative method
- **Ease in Contraceptive Decision Making at Time 1:** Compared to women who receive usual care alone, women randomized to the decision aid arm will report greater ease in contraceptive decision making at Time 1

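### The sensitivity models for T3 satisfaction, T2 knowledge and T2 decisional conflict adjust for counselling and consent arising after randomisation, so they cannot test the robustness of the intervention effect

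*Combined protocol and SAP*

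**What the plan says.** Primary and Secondary Hypotheses sets the main analysis: intention to treat, linear or logistic regression, adjusted for site. The co-primary outcomes are knowledge and decisional conflict at T1. Satisfaction with decision-making at T3 is secondary. Knowledge and decisional conflict at T2 are exploratory, and Exploratory Outcome Measures says they are collected to see whether the aid's effect lasts.

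Exploratory Hypotheses then adds two sets of models.

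- **T3 satisfaction:** "We will run additional sensitivity analyses to test robustness of the intervention effects after adjusting for differences in" a list that includes provider sterilization counselling, "Provider contraceptive counseling between T1 and T3" and "Medicaid consent signed between T1 and T3".
- **T2 knowledge and T2 decisional conflict:** models with the same stated aim, to "test robustness of the intervention effects after adjusting for differences in" the T1-to-T2 versions, including "Medicaid consent signed between T1 and T2".

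Elsewhere the plan describes how the aid could reach these variables. Intervention participants receive a summary sheet "which they are encouraged to share with their healthcare provider". On consent, "women in the intervention arm who remain interested in undergoing sterilization as they proceed through pregnancy must complete the consent process".

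**The concern.** A sensitivity analysis tests robustness when it estimates the same quantity as the main analysis under different assumptions. Adjusting for something the treatment may itself have changed alters the quantity. If the aid works partly by prompting provider discussions, or by changing who goes on to sign the consent, adjustment removes that part of the effect. If counselling or consent also shares causes with the outcome, such as strength of desire or engagement with care, adjustment makes the arms non-comparable on those causes.

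At stake is the reading of one secondary and two exploratory results. A real effect on satisfaction that runs through better discussions could shrink on adjustment and look fragile, or an effect could look stronger than it is. The plan gives no rule for interpreting a discrepancy, so nothing in it guards against either reading.

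**Working it through.** **1. Time order.** Baseline, Intervention, and Time 1 Assessment places randomisation after the baseline interview and before T1. Anything dated from T1 onwards is therefore post-randomisation. For T3, the sterilization-counselling covariate is a composite meant to separate out women already counselled at baseline, so it targets counselling after randomisation.

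**2. Path from the aid.**

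| Covariate | Link to the aid in the documents |
|---|---|
| Counselling | The summary sheet goes to intervention participants only. Recruitment says providers are told it is to help discussion at visits. The trial records whether it was shared. |
| Medicaid consent | Usually completed at 24-32 weeks (Usual care arm), after the aid is used before 24 weeks. Only women still interested go on to sign. Secondary hypothesis (a) says the aid lowers selection of sterilization. |

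**3. The plan's own caution.** Exploratory Analyses in Specific Subset(s) of the Sample says that comparisons within subsets have lost the protection of randomisation and need confounder control. One of those subsets is women who had sterilization counselling. Restricting on counselling carries the warning, but adjusting for post-T1 counselling in the sensitivity models does not.

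**4. The plan's design figure, for scale.** n per arm = 2(z0.9875 + z0.80)²/d² = 2(2.2414 + 0.8416)²/0.36² = 146.7, so 147, and 147/0.85 gives 173. The t-based version needs 148, and 148/0.85 rounds up to the stated 175. The sample size reproduces and is not in question.

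**5. Illustrative size.** The documents give no figure for the aid's effect on counselling or consent, so every input here is an assumption. A is arm, U an unmeasured common cause with distribution N(0,1), and M the covariate:

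- logit P(M=1) = 0.2 + s(A - 0.5) + 0.8U
- Y = 0.20A + 0.30M + 0.4U + e, with e having SD 1

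The total effect is 0.20 + 0.30 × (change in uptake). The adjusted effect is the coefficient of A in a linear model with A and M. Simulated results (4,000,000 records per row):

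| Uptake, control to aid | Total | Adjusted | Adjusted minus total |
|---|---|---|---|
| 45.6% to 62.8% | 0.252 | 0.152 | -0.10 |
| 62.9% to 45.6% | 0.148 | 0.248 | +0.10 |
| 50.0% to 58.6% | 0.226 | 0.175 | -0.05 |
| 58.7% to 50.0% | 0.174 | 0.225 | +0.05 |
| 52.3% to 56.6% | 0.215 | 0.190 | -0.025 |
| no shift | 0.199 | 0.199 | 0 |

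Splitting the first row: moving from the total effect to the direct effect accounts for 0.252 - 0.200 = 0.052, and the common cause accounts for 0.200 - 0.152 = 0.048. About half of the gap is a change of estimand and half is bias. If M has no effect on Y, the true 0.20 still becomes about 0.15 or 0.25 at the 17-point shift, from the common cause alone. Without the common cause, the adjusted value is the direct effect of 0.20.

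A second model with stronger assumptions (covariate effect 0 or 0.5, common-cause coefficient 0 or 0.7, shifts up to about 20 points) gives gaps from about -0.13 to +0.13 SD, against the design effect of 0.36 for decisional conflict. With a true total effect of zero and a non-causal covariate, it gives a spurious effect of about 0.065 in size when uptake shifts by about 18 points.

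**6. Availability of one covariate.** The Variables table lists "Received any provider contraceptive counseling" at BL and T2 only, and Covariates and Baseline Characteristics agrees. Sterilization counselling and consent are also asked at T3.

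**The case against.** The strongest reply is that these are exploratory models on which no alpha, decision rule or primary conclusion depends, and that the aid's effect on the covariates is plausible rather than shown. Counselling and consent are usual care in both arms. The sterilization-counselling item records only whether a discussion took place, and the summary sheet may change what is said rather than whether it is said. If uptake does not differ by arm, the bias vanishes. T2 is timed to follow the usual signing of the consent, so asking whether the effect persists given later care is reasonable. The plan also has a separate robustness model using baseline characteristics, limited to significant imbalances associated with the outcome.

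Most of this stands, and it limits how far the point reaches. Several stronger readings are tempting, and the documents do not support them:

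- **That the randomised effect itself is biased.** The site-adjusted intention-to-treat estimate is specified separately and is untouched, as are both T1 co-primary analyses.
- **That all T2 and T3 outcomes are affected.** Only three are. Method selected at T2, method used at T3, ease, certainty, confidence and subsequent pregnancy have no such adjustment.
- **That the error is known to be large.** The 17-point shift is an assumption, and about half of that gap is direct versus total effect. The largest illustrative gap (0.10) is below the standard error of an arm difference at about 149 evaluable per arm, √(2/149) = 0.116 SD. That comparison does not remove the problem, because both estimates come from the same women and the gap is systematic.
- **That the contraceptive-counselling covariate cannot be built at all.** The T1-to-T2 part can be built. Only T2 to T3 is missing.

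What the reply does not answer is the stated purpose. The models are presented as tests of robustness, not as direct-effect or mediation analyses, and no control for common causes is planned for them.

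**Conclusion.** The point holds for T3 satisfaction with decision-making, T2 knowledge and T2 decisional conflict. Their post-T1 adjusted models do not estimate the total randomised effect if the aid shifts counselling or consent, which the plan itself anticipates, so they cannot confirm or undermine the intention-to-treat result. Direction and size are unknown. Under the main illustrative assumptions the gap runs from zero (no shift) to about 0.10 in either direction (17-point shift), on a direct effect of 0.20. This should be fixed before analysis, but it does not threaten the trial's main conclusions.

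**What to change.** - Remove the T1-to-T2 and T1-to-T3 counselling and consent covariates from the robustness analyses of the three outcomes, and keep arm plus site as the effect estimate.
- If counselling or consent is to be adjusted for as a robustness check, use only the baseline answers, which are already collected before randomisation.
- If the post-T1 models are kept, report post-T1 counselling and consent by arm, label the models as exploratory mediation or direct-effect analyses, include baseline confounders, extend the subset section's caution to them, and state that they are not used to judge robustness.
- Redefine the contraceptive-counselling covariate for T3 as covering T1 to T2, or drop it.

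The cost is SAP wording. No new data are needed and the randomised comparison loses nothing. The question of how the aid works moves to a labelled analysis.
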